**Methods and analysis:**

This ongoing study uses a cohort design, recruiting participants from the Northern Ireland Cohort for the Longitudinal study of Ageing and the Harmonised Cognitive Assessment Protocol study. Participants (n=400 at each wave) will be aged ≥65 years and have the capacity to provide written informed consent. Measures include device-measured physical activity (Actigraph wGT3XP-BT), environmental location data (Global Positioning System, Qstarz BT-Q1000XT), linked to a battery of neuropsychological tests, including the Mini Mental State Examination and the Centre for Epidemiological Studies Depression Scale. Blood-derived biochemical, genetic and epigenetic data will be included in multimodal analyses. These data will be integrated with urban environment Geographic Information System data and analysed using causal inference and mediation methods to investigate plausible mechanistic pathways.

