**Ethics and dissemination:**

This study has been approved by the Queen’s University Belfast, Faculty of Medicine, Health and Life Sciences Research Ethics Committee (MHLS 21_72). Alongside peer-reviewed publications in high-ranking international journals, dissemination activities include conference presentations, project videos, working papers, policy briefing papers, newsletters, summaries and case study stories.

STRENGTHS AND LIMITATIONS OF THIS STUDYA strength is the use of device-measured physical activity and the integration of Geographic Information System and Global Positioning System data, combined with cognitive health data.The large sample enables an in-depth analysis of the causal mechanisms of cognitive decline, mild cognitive impairment and dementia in older adults.The environmental exposure data facilitate the analysis of the impact of co-exposures on cognitive health outcomes and their mechanistic pathways.A limitation is the generalisability of results, due to participants residing in Northern Ireland, and the age restriction of over 65 years.

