#### Sample size

The NICOLA-HCAP assessment will be offered to the NICOLA participants aged ≥65 years, with a random sample of 50% of those living alone (n=1695) and a random sample of 50% of those living in a partnership or with a sibling etc. (n=2401). The response rate for the NICOLA-HCAP is expected to be approximately 80% and assuming a selection rate of ~1 in 3 to achieve the target of 1000 participants. Of 1000 NICOLA-HCAP participants, there is an anticipated uptake to the current study of ~40% (n=400).

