#### Mediation analysis

Associations of environmental attributes (GIS data) with lifestyle behaviours and cognitive health will be estimated using multilevel modelling in a structural equation modelling framework,^54^ which is able to account for administrative unit-level and person-level (repeated measures) clustering and is appropriate for data with different distributions.^55^ Contemporary guidelines on discerning general from specific context effects will be followed.^56^ Plausible confounders will be identified using a pre-specified conceptual framework in conjunction with rules governing appropriate covariate selection and depending on the mechanism proposed, will be modelled as either a time-non-varying covariate, moderating or mediating effect as appropriate.^57^ Measurement of cognitive function took place in Waves 1+2 of NICOLA as well as the HCAP (in 2021), (26) yielding data that is amenable to use in a latent change score mediation within a multilevel SEM framework, satisfying the temporal ordering assumption for mediation analyses.^54 58 59^ Current guidelines on reporting SEM analyses will be followed.^60^ As a sensitivity check, an alternative approach to mediation from the causal inference literature will be used to decompose the total effect of the environment on cognitive function into direct, indirect and interactive effects.^61^ Based on a bias-corrected bootstrapping test of mediation, with 2000 bootstrap samples, and assuming a small (simulated at 0.14) effect size for both the path from environment to mediator and from mediator to environment, a sample size of approximately 462 would be required for a power of 0.8.^62^ Complementary to this, to further inspect putative causal relations between mediators and cognitive function, a 2-wave latent change score model (as previously used)^63^ will be used on a subset of Wave 1 NICOLA and NICOLA-HCAP respectively. Traditional bias-corrected bootstrapping will be used to determine whether lifestyle behaviours mediate the association between environmental exposures and cognitive outcomes. We will employ two strategies to mitigate collinearity, either: (1) composite measures of collinear variables or (2) the residual error term from preliminary bivariate regressions, will be included in multiple predictor models. Missingness will be assessed and, if missing at random or completely at random, will be addressed by full information maximum likelihood estimation for the mediation analyses.

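### The mediation power statement calls for about 462 participants, the study plans 400, and the gap is not reconciled; for device-measured mediators power at 400 is about 0.71

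*Protocol article*

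**What the plan says.** The power statement is in the Mediation analysis section of the protocol article. Its test is described as follows: "Based on a bias-corrected bootstrapping test of mediation, with 2000 bootstrap samples". The effect size is given by "assuming a small (simulated at 0.14) effect size for both the path from environment to mediator", and the conclusion is that "a sample size of approximately 462 would be required for a power of 0.8". The two paths are described as "both the path from environment to mediator and from mediator to environment".

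The planned size is given in two other places. The Sample size section starts from 1000 NICOLA-HCAP participants and says "there is an anticipated uptake to the current study of ~40% (n=400". The Abstract says "Participants (n=400 at each wave) will be aged ≥65 years".

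Three further statements bear on the point:
- The Introduction names physical activity as a mediator between the urban environment and cognitive health, and the accelerometry section heading lists it among the mediating variables.
- Under Study procedure, the accelerometer and GPS are issued only to people taking part in the current study.
- The accelerometry section excludes participants without enough valid wear time, without giving an expected loss.

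**The concern.** The article prints a requirement and a target for the same study, and the target is 62 lower (62/462 = 13%). It does not acknowledge the shortfall, name a larger sample for the mediation models or give the power at 400. The strengths list, meanwhile, says that "The large sample enables an in-depth analysis of the causal mechanisms of cognitive decline". A reader who sees the power sentence cannot tell whether the planned study meets it.

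What is at stake is the chance of detecting the pathway that the Introduction singles out, environment to physical activity to cognition, at the effect size the authors chose as their planning value.

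The power sentence has a second, smaller defect. It runs the second path from the mediator back to the environment, whereas a mediation test needs the path from mediator to cognitive outcome. The same section later describes the test as one of mediation between environmental exposures and cognitive outcomes, so this is a slip in the label.

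**Working it through.** **Inputs from the article.** Both paths 0.14; bias-corrected bootstrap; 2000 resamples; target power 0.8; required n about 462 (Mediation analysis). Planned n = 400 (Abstract; Sample size).

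**Assumed, because not stated.** Two-sided alpha 0.05 (a 95% interval), a single-level model with one mediator, no direct effect, complete data.

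**Model.** X ~ N(0,1); M = 0.14·X + e; Y = 0.14·M + e. The indirect effect is a·b. A pathway counts as detected when the 95% bias-corrected bootstrap interval for a·b excludes zero. There were 4000 simulated data sets per sample size.

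**Step 1: reproduce the plan's figure.** At n = 462 power is 0.787 with residual variance 1 and 0.803 with standardised variables. The stated 462 for power 0.8 therefore reproduces, which also supports the alpha assumption.

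**Step 2: power at the planned size.**

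| n | Power, bias-corrected bootstrap |
|---|---|
| 462 | 0.79 to 0.80 |
| 400 | 0.71 (0.712 in both variants) |

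The Monte Carlo standard error at 400 is √(0.71 × 0.29 / 4000) = 0.007. Other runs of the same model gave 0.78 and 0.82 at 462, and 0.69 to 0.72 at 400. The chance of missing a true pathway of this size rises from about 20% to about 29%.

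**Step 3: cross-check with a closed form.** The joint-significance approximation is Φ(0.14·√(n−2) − 1.96) × Φ(0.14·√(n−3) − 1.96).
- n = 462: 0.851 × 0.851 = 0.72.
- n = 400: 0.798 × 0.797 = 0.64.

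The percentile bootstrap gives 0.70 at 462 and 0.61 at 400. Both methods are less powerful than the planned test, but the drop from 462 to 400 is of the same order, about 9 points.

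**Step 4: path detectable with power 0.8 at 400.** Power depends mainly on path × √n, so the path scales as 0.14 × √(462/400) = 0.14 × 1.075 = 0.150. As a check, simulated power at n = 400 with both paths at 0.152 is 0.79.

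**Step 5: direction of the wear-time exclusions.** The article gives no loss rate, so these are illustrations only. An assumed 10% loss (n = 360) gives 0.66, and an assumed 20% loss (n = 320) gives 0.59.

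**Step 6: which mediators are tied to 400.** Monitors go only to current-study participants, so mediators derived from the accelerometer or GPS exist for about 400 people at a wave. Full information maximum likelihood, planned for missing data, does not create mediator information for people who never wore a device. Other mediators are not tied to 400 in this way. The social variables in Table 1 come from NICOLA, and the Mediation analysis section does not say which sample each model uses.

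**The case against.** The strongest reply is that 400 is not the only sample in the article. NICOLA-HCAP has 1000 participants, NICOLA over 8000, and biochemical markers exist for 3082. GIS data can be joined to home addresses without a GPS device, and cognition was also measured in NICOLA Waves 1 and 2. A model with a mediator drawn from those sources could exceed 462. This stands. A reader might infer that all the planned mediation work is underpowered; the documents support that only for device-measured mediators.

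A reader might also infer that the article promises power of 0.8 and fails to deliver it. It does not. It says what would be required and never claims that 400 meets it. The 462 is not an arithmetic error either.

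Wave 2 does not settle the matter. One could argue that the panel measured twice will be smaller than 400. But refreshment participants are also to be invited, so the number of distinct people could be larger. For instance, with an assumed 75% return and 400 at each wave, 300 would be measured twice, but 400 + 100 = 500 people would be seen at least once. No retention figure is given, and wave 2 depends on funding.

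It is tempting to add the false discovery rate correction as a further loss. That sentence closes the Compositional data analysis section, and nothing shows that it reaches the mediation tests. It is likewise conjecture that a null result would be read as evidence of no pathway; the article plans no such reading.

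Finally, this is an observational cohort whose size follows from expected uptake in a parent study, and it has other analyses. That tempers the weight of the point but leaves the two figures unreconciled.

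**Conclusion.** The point holds for mediators measured by the study's own accelerometer and GPS. Against the stated requirement of about 462, the planned 400 gives power of about 0.71 in place of 0.8, a loss of about 9 points; equivalently, the detectable path is about 0.15 and not 0.14. The result rests on two-sided alpha 0.05, a single-level model and complete data. Wear-time exclusions would reduce power further; clustering by area is outside the calculation and would generally do the same. The article does not permit either effect to be quantified.

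For mediators held in the wider NICOLA-HCAP or NICOLA samples, no shortfall is shown. The mislabelled second path is a plain wording error. This is a moderate shortfall that should be stated openly; it does not undermine the design.

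**What to change.** In the Mediation analysis section:

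1. Name the analysis sample, and its expected size, for each mediation model.
2. For the device-measured mediators, replace the statement about 462 with the position at the planned size, for example: *For mediators derived from the accelerometer or GPS (planned n = 400), power to detect an indirect effect with both paths equal to 0.14 is about 0.71 (bias-corrected bootstrap, 2000 resamples, two-sided alpha 0.05, single-level model, complete data); power of 0.8 requires both paths to be about 0.15. Power will be lower to the extent that monitor data are unusable.* If the authors used another alpha, they should state it and recompute.
3. Correct the second path so that it runs from mediator to cognitive outcome.

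No fixed number of participants with valid monitor data, or returning at wave 2, should go into the text unless the authors have a source for it.

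The cost is a less favourable stated power. No extra recruitment or change of design is needed.

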Healthy urban environments can also support social activity including social interactions which are important for preventing dementia.^4^ Conversely, urban environments which offer few opportunities for social connections, social interactions and sociable behaviours negatively impact cognitive health and accelerate cognitive decline.^15^ Meanwhile, many attributes of the social environment (such as crime and safety, social disadvantage, social capital, disorder and civic participation) predict both positive and negative outcomes for cognitive health.^16^ The social environment encompasses social relationships,^17^ which are also associated with dementia risk.^18^ Supportive social environments also offer contexts for provision of social support and social interaction, both of which are also associated with dementia.^18^,^20^ Livingston and colleagues noted the potential for an 8% reduction in the risk of dementia if social isolation in later life were to be eliminated.^4^ Therefore, it is important that urban environments are designed to support social activity.

However, to date, the literature reports inconsistent associations between cognitive health outcomes and environmental exposome factors. This may be because elements of the environmental exposome are being studied in isolation, with little regard for the complex interrelationships between environmental variables.^21^ This may also be relevant for physical activity particularly in the urban environment, where other features of urban design bring with them potential negative effects on biomarkers and cognitive health.^22^

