#### Molecular mediating data

Blood-derived biochemical data is available for 28 markers for 3082 participants within the NICOLA cohort (see online supplemental table 1). Blood-derived biochemical, genetic and epigenetic data will be combined with demographic, clinical, behavioural and environmental data for multimodal analyses. DNA was extracted from buffy coats by Eurofins Scientific, quantified using PicoGreen, normalised and aliquoted into multiple working volumes in cryvials to minimise freeze-thaw cycles and maximise the quality of DNA. Genotype data was generated on the Infinium CoreExome-24 array (Illumina, USA), with standard quality control applied and imputation to the 1KGP3, HRC and TopMed reference panels. Kinship matrices have been generated. Association analysis will be performed, but the primary utility of genetic data is to enable Mendelian Randomisation to explore causal inference and to help interpret epigenetic findings. DNA methylation is the primary molecular ‘ome’ of interest for this study, due to its ability to dynamically changes in response to medical, lifestyle and environmental changes. Methylation data were generated using Infinium MethylationEPIC 1.0 BeadChips (Illumina, USA) after bisulphite treatment with the EX Zymo Methylation Kit (Zymo Research, USA) following manufacturer’s instructions. Participant samples were randomly distributed across 249 arrays, with quality control including eight duplicate samples (n=16) and evaluation of the bisulphite treatment conversion efficiency, dye specificity, hybridisation and staining. Samples were initially assessed using GenomeStudio v2011 and the BeadArray Controls Reporter software platforms (Illumina, USA). Crossreactive probes, those located within 3 bp of common SNPs, and those on sex chromosomes will be excluded from primary analyses. Unreliable probes and samples will be removed before association analysis is performed. Proportional white cell counts will be estimated for CD8+T, CD4+T and CD19+B lymphocytes, CD56+ natural killer (NK) cells, CD14+ monocytes and CD15+ granulocytes using the Houseman method.^47^ Beta values were generated before M values were derived for all sites. P values were computed using the limma method for each site.^48^ Hierarchical linear models from the limma package were employed and fitted using Bayes approach on the derived M values. P values were generated for each of the four differential analyses conducted. RnBeads will be used to perform EWAS with single site resolution with multivariate regression analysis performed for quantitative traits adjusting for sex and age. RNA was collected in Paxgene tubes and extracted by Eurofins with quantitation performed on a Bioanalyser. Samples with a RIN >6 underwent sequencing using either a whole transcription or AmpliSeq technology for library preparation on an Ion Chef and subsequent sequencing on an Ion Proton or Ion GeneStudio S5 system (Life Technologies, USA). Transcriptome-wide association analysis will be performed, but the primary utility of this dataset for this project is to help understand the functional impact of epigenetic changes. Individual ‘omic’ analyses, exploring contributions from individual omics as well as a combined model, will be conducted with Mendelian Randomisation employed to explore causal influences with a composite multimodal biomarker signature generated. This project will provide more knowledge on the mechanistic pathways underlying how the urban environmental exposome affects cognitive outcomes in older adults, identify which environmental impact has the most biological impact, and has potential to identify a multiomic signature for people at higher risk of cognitive decline.

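### Residualising one collinear exposure on another leaves the separate effects as imprecise as before and assigns the shared association to whichever exposure was not residualised

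*Protocol article*

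**What the plan says.** The Mediation analysis section names two ways of handling correlated exposures. The first combines them into composites. Under the second, "the residual error term from preliminary bivariate regressions, will be included in multiple predictor models". It does not say which exposure is regressed on which, whether one or both are replaced by residuals, or how the coefficient of an exposure left in its raw form will be read.

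Attribution between exposures matters elsewhere in the article. The Introduction suggests that earlier results may be inconsistent because "elements of the environmental exposome are being studied in isolation, with little regard for the complex interrelationships between environmental variables". The strengths list after the abstract says: "The environmental exposure data facilitate the analysis of the impact of co-exposures on cognitive health outcomes and their mechanistic pathways". The Molecular mediating data section expects the project to "identify which environmental impact has the most biological impact".

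**The concern.** Collinearity is a problem because the data hold little information on the separate effect of each exposure. A remedy has to add information, shrink the estimates or change the question. Replacing an exposure by its residual on another does none of these for the residualised exposure, because it only rewrites the same linear model. For the other exposure it changes the question without saying so: its coefficient absorbs the association that the two share.

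The result then turns on an analyst's choice that the article does not fix. With the same data, whichever exposure stays raw can look like the active one. If that coefficient is reported as an independent effect, the study may name the wrong feature of the urban environment.

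**Working it through.** **The section's only figure.** The article uses "Based on a bias-corrected bootstrapping test of mediation, with 2000 bootstrap samples", "assuming a small (simulated at 0.14) effect size for both the path from environment to mediator" and the same for the second path, and concludes that "a sample size of approximately 462 would be required for a power of 0.8". Simulating that test (1000 datasets, two-sided 0.05, no direct effect) gives power 0.782 at N=462, with a Monte Carlo standard error of about 0.013. This is close to the stated 0.8. The present point does not depend on that figure, but borrows 0.14 as an illustrative slope.

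**Inputs.**
- From the article: n=400 (Sample size section) and slope 0.14.
- Assumed: correlation r between the exposures (none is given), two-sided alpha 0.05, standardised exposures, residual SD 1.

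**One exposure residualised.** Let Y = b1·X1 + b2·X2 + error, and X2 = d·X1 + e2, where d is the slope from the preliminary regression (d = r for standardised exposures). Substituting gives Y = (b1 + d·b2)·X1 + b2·e2 + error. Three things follow.
1. X1 and e2 are uncorrelated, so the variance inflation factor falls to 1 from 1/(1 − r²), for example from 2.78 at r=0.8.
2. The coefficient of e2 is b2, with the same standard error as X2 in the joint model: 0.05/√(1 − r²), about 0.058, 0.063, 0.083 and 0.115 at r=0.5, 0.6, 0.8 and 0.9. Least-squares runs agree to rounding error.
3. The coefficient of X1 is b1 + r·b2, with standard error 1/√400 = 0.05.

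**Size when X1 is truly null (b1=0, b2=0.14).** The chance that X1 is declared significant is approximately Φ(r·0.14/0.05 − 1.96).

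| r | X1 coefficient, r × 0.14 | Φ(·) | Simulated | Joint model |
|---|---|---|---|---|
| 0.5 | 0.070 | Φ(−0.56) = 29% | about 28% | about 5% |
| 0.6 | 0.084 | Φ(−0.28) = 39% | about 39% | about 5% |
| 0.8 | 0.112 | Φ(0.28) = 61% | about 59% | about 5% |
| 0.9 | 0.126 | Φ(0.56) = 71% | about 71% | about 5% |

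Repeat simulations agree within two percentage points. Residualising X1 on X2 instead returns X1 to about 5% at every r.

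**Both exposures residualised on each other.** The two residuals correlate at −r, so the collinearity keeps its size. With b1 = b2 = b, each coefficient becomes (b + r·b)/(1 − r²). At b=0.14 and r=0.9 this is 0.266/0.19 = 1.40 instead of 0.14.

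**With a confounder Z in the model.** The same substitution gives X1 the coefficient b1 + d·b2, where d is still the unadjusted slope of X2 on X1. The confounder-adjusted total effect of X1 is b1 + dz·b2, where dz is the slope adjusted for Z. They differ by (d − dz)·b2. Illustration with assumed correlations of 0.8 between the exposures and 0.7 between Z and each exposure: dz = (0.8 − 0.49)/(1 − 0.49) = 0.608. With b1=0 and b2=0.14 the residual option gives 0.112. The adjusted total effect is 0.608 × 0.14 = 0.085, and the independent effect is 0.

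**The case against.** The strongest defence is causal order. If X1 lies upstream of X2, as street or housing density may for traffic pollution, the raw coefficient of X1 could be meant as a total effect, and the significant results above would then be power. The article leans that way in places. Its causal loop diagram separates urban design from environmental by-products, and Table 1 treats road and transit densities as proxies for pollution. Order and interpretation may also be set out in a fuller plan. Part of this stands: the error rates apply only when the coefficient is read as adjusted for X2. It does not rescue the rule as written, because the step is presented as a cure for collinearity with no order attached. In a confounder-adjusted model, a bivariate residual does not in general give the adjusted total effect either.

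A reader might also infer stronger claims that the material does not support.
- That collinearity is not reduced at all. With one exposure residualised, the nominal correlation does fall to zero; it keeps its size when both are residualised on each other.
- That the intervals are falsely narrow. The standard error of 0.05 is right for the changed quantity.
- That X1 takes the whole effect of X2. It takes only slope × b2.
- That X1 always gets its plain unadjusted coefficient. This holds only without covariates.
- That error rates near 90% are to be expected. They need a slope of about 0.2 with r near 0.8, and 0.2 exceeds the plan's own 0.14.

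**Conclusion.** The concern holds in this limited form. The residual option removes the nominal correlation between the entered terms, but leaves the separate effect of the residualised exposure exactly as imprecise as in the joint model. It hands the shared association to the exposure left raw. At the plan's own effect size and n=400, a null exposure read as an independent effect would be declared significant in roughly 28% to 71% of runs for r from 0.5 to 0.9, instead of about 5%.

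The algebra is exact for linear models. The percentages rest on assumed correlations, a two-sided 0.05 test, unit residual SD and the use of 0.14 as a slope. The identity carries over to linear paths in the structural equation model, but the multilevel model was not simulated. The composite option is not affected. A reader might infer that separating co-exposures is the study's sole purpose. It is not, since the key objective is mechanistic pathways, but the stated interest in co-exposures and in which environmental impact has most effect makes attribution matter enough to correct the rule.

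**What to change.** Delete the residual option from the Mediation analysis section. For exposures that cannot be separated, keep the composites already listed and pre-specify them. Otherwise enter the exposures jointly, and report their joint effect where the individual effects are too imprecise to interpret.

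Where a causal order between two exposures is pre-specified and a total effect is wanted, estimate it by leaving the downstream exposure out of the confounder-adjusted model, and label the result a total effect. Ridge or mixture methods are optional checks, not a requirement.

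The change is a sentence or two. The price is wider intervals for individual collinear exposures: at r=0.8 and n=400, under the assumptions above, the standard error for X1 is about 0.083 in the joint model against 0.050 under the residual option. That width reflects what the data can say about the separate effects.
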